**11.1.2.4. Cardiac assessment:**

The ECG assessment should be performed to check for any changes resulting from COVID-19 and investigational medications. The QTc will be checked on all ECG's.

The participant must rest for a minimum of 5 minutes before the ECG is performed.

**11.1.3. Patient reported outcomes**

Results questionnaires reported by patients (EQ-5D-5L and Dyspnea scale - WURSS-11) will be answered by the participants before the study team carries out any study or clinic evaluation to avoid influencing the participants' responses. Study coordinators will review the participant's responses immediately after the participant completes the questionnaires to ensure that all questions are answered.

**Questionnaire EQ-5D-5L:** The EQ-5D-5L questionnaire consists of 5 questions, each with five levels (eg, no problems, mild problems, moderate problems, serious problems and extreme problems) representing 5 health domains: mobility, self-care, activities symptoms, pain and / or discomfort, and anxiety and / or depression. The EQ-5D-5L questionnaire also includes a visual analog scale that records the self-assessment of the participant's health status, graded on a scale ranging from 0 to 100, with higher scores indicating greater health-related quality of life. Participants must complete the EQ-5D 5L questionnaire as indicated in the event schedule.

**WURSS-11 scale** (Wisconsin Upper Respiratory Symptom Survey -11):

<https://www.fammed.wisc.edu/files/webfm-uploads/documents/research/wurss-11.pdf>

**11.2. Adverse Events for Brazil****11.2.1. Definition of Adverse Events for Brazil**

An adverse event is any unfavorable medical occurrence suffered by a patient or a participant in a clinical study who has received a drug that does not necessarily have a causal relationship to that treatment. An AE can therefore be any sign (including an abnormal laboratory finding) or unfavorable and unintended symptom or disease temporally related to the use of a medicated product (under investigation), whether related to the medicated product (under investigation) or not.

That includes:

(1) any new clinical sign or symptom, clinically significant abnormality of physical examination or newly diagnosed event that occurs during the reporting period for AEs, including signs or symptoms associated with an underlying condition that were not present prior to the reporting period. reporting of AEs;

(2) a pre-existing condition that worsened in severity or frequency or changed character after the participant signed the informed consent form during the reporting period for AEs; and

(3) complications that occur as a result of interventions required by the protocol. An AE can arise from any use of the drug under investigation (eg, use outside the indication, use in combination with another drug) and with the use of any route of administration, formulation or dose, including an overdose. AEs can also be any side effects, damage, toxicity or sensitivity reactions that may be experienced by a participant in this clinical study.

For the purposes of this protocol, events that will not be considered AEs include:

- Signs or symptoms expected to fluctuate from a pre-existing medical condition (eg, tremor in a participant with Parkinson's disease; migraine episodes) that did not worsen in severity or frequency or change character during the reporting period for AEs;
- Surgeries or medical procedures are not AEs; however, the clinical condition (new or worse) that led to the surgery or medical procedure is the reported AE (eg, for appendicitis resulting in appendectomy, appendicitis must be reported as the AE);
- Overdose without clinical signs or symptoms;
- Pregnancy.

### **11.2.2. Adverse Event Reporting for Brazil**

AEs, including serious adverse events (SAEs), will be collected throughout the study period, from the moment the participant signs the informed consent form and until the End of Study visit. All AEs still present at the time of completion of the study will be monitored by the investigator through contact with the participant until resolution or stabilization, or until the participant loses follow-up and he can no longer be contacted. The result must be documented in the participant's source documents. The investigator must report all AEs that occur after the reporting period specified in the protocol if, according to the investigator's assessment, there is a reasonable possibility that the AEs is related to the product under investigation or any study procedure.

Participants will be asked to complete Surveys (Daily Survey and Exit Contact Survey) that include information on any symptoms that they are experiencing. In addition, AE review by a staff member (via telephone, Telehealth, or text messaging) will be performed.

If the participant reports an AE, it is the investigator's responsibility to obtain sufficient information to assess causality. This may require additional laboratory tests, physical examinations, telephone contacts, etc.

To avoid bias in collecting AEs, participants should be asked to answer a neutral question, such as "How are you feeling?" It is also important to ask the participant in a non-biased way about changes in their health or use of concomitant medication since their last visit. This information must be collected before evaluations are carried out on all study visits. In addition, any symptoms or conditions reported during the assessments and considered clinically significant by the investigator will be assessed as AEs.

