**Duration:**

90 days of clinical follow-up per participant

Enrolment and completion TBD based on the observed recruitment rate

**Proposed sites:** Concurrent with the US site (TOGETHER 1), Brazil (TOGETHER 2), we will work together to generative comparative data. Interventions for TOGETHER 1, 2 and 3 may differ depending on feasibility, evolving epidemiology and the evidence on interventions, and appropriateness of interventions in the local environments.

| Harmonized protocol document                                                          |
|---------------------------------------------------------------------------------------|
| Short title: Outpatient Management of SARS-CoV-2 for High-Risk Adults in LMICs |

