## 2. Schedule of Activities

### 2.1. Schedule of activities for Brazil

| FLOWCHART                                                                                    | STUDY VISIT SCHEDULE                             |                                                     |                               |                              |                               |                              |                               |                               |                               |                               |                                                        |
|----------------------------------------------------------------------------------------------|--------------------------------------------------|-----------------------------------------------------|-------------------------------|------------------------------|-------------------------------|------------------------------|-------------------------------|-------------------------------|-------------------------------|-------------------------------|--------------------------------------------------------|
|                                                                                              | Screening and treatment period                   |                                                     |                               |                              |                               |                              | Post-treatment period         |                               |                               |                               |                                                        |
|                                                                                              | Screening 
Visit
(D-minus 1) | Baseline and
randomization
 D-0 | D1-2 
+1 day | D-3 
+1 day | D4-8 
+1 day | D-9 
±1 day | D-10 
±1 day | D-14 
±1 day | D-28 
±2 day | D-56 
±5 day | D-90 or Early
Termination
 ±5 days |

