| Adverse Events (AEs)                                                                         |                                                  | X                                     | X                             | X                            | X                             | X                            | X                             | X                             | X                             |                               |                                                        |
| Dyspnea Scale (WURSS-11)                                                                     |                                                  | X                                     | X                             | X              | X               | X              | X               | X               |                               |                               |                                                        |
| Tisdale scale                                                                                |                                                  | X                                                   |                               |                              |                               |                              |                               |                               |                               |                               |                                                        |
| EQ-5D-5L                                                                                     |                                                  | X                                     |                               |                              |                               |                              |                               |                               | X               |                               | X                                        |

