### 3.3. **Benefit/Risk Assessment**

**There is equipoise as to whether the *in vitro* efficacy of any drug will translate into efficacy to prevent LRTI.** COVID-19 disease can be unpredictable in its severity, but a 3.4% mortality rate has been observed among clinical pneumonia cases. The elderly (>60 years) and those with medical comorbidities are at highest risk of poor outcomes. Moreover, transmission in younger persons amplifies infection in communities, putting susceptible persons at risk. There is no proven drug for treatment of those with COVID-19 disease.

**QT prolongation:** Azithromycin and LPV/r are widely used throughout Brazil without the requirement of QT measurements prior to initiation. LPV/r has been reviewed by CredibleMeds (crediblemeds.org) but the evidence available at this time did not result in a decision for it to be placed as a risk medicine for QT prolongation and Torsades de Pointes. Azithromycin has been associated with QT prolongation. However we will exclude patients with a baseline QTc interval of > 470 ms in males, and > 480 ms in females.

**LPVr use in undiagnosed HIV-positive patients:** Ten days of LPV/r monotherapy is unlikely to cause resistance (high barrier to resistance) and is effective for viral suppression. The risk of HIV-associated immune reconstitution inflammatory syndrome (IRIS) is possible, and the time of onset varies from days to months after antiretroviral initiation. Ten days of LPV/r potentially carries a low risk of unmasking IRIS in undiagnosed HIV-positive patients. Should IRIS occur, it will be recorded as a serious adverse event (SAE). Testing for HIV prior to enrolment is not pragmatic as it exposes health care workers to SARS-CoV-2 infection and there is no referral pathway for newly diagnosed HIV-positive patients with SARS-CoV-2 co-infection. In this study we minimise interaction between study staff and patients using Telehealth.

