#### **10.1.3. Day 28 (+/- 5 days)**

Participants will be followed-up via Telehealth, text messaging, or telephone:

- EQ-5D-5L
- Review of AEs, clinical symptoms, and hospitalization

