#### **10.1.4. Day 56 (+/- 5 days)**

Participants will be followed-up via Telehealth, text messaging, or telephone:

- Review of clinical symptoms, and hospitalization

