#### **10.1.5. Day 90 or early termination (+/- 5 days)**

Participants will be followed-up via Telehealth, text messaging, or telephone:

- Review of clinical symptoms, and hospitalization
- EQ-5D-5L

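### Section 11.2.2 collects adverse events to the End of Study visit, but no AE review is scheduled after Day 28 or at early termination, so late capture is contradictory and likely uneven

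*Protocol*

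**What the plan says.** Section 11.2.2 sets the collection period for AEs and SAEs: they "will be collected throughout the study period, from the moment the participant signs the informed consent form and until the End of Study visit". The synopsis gives "90 days of clinical follow-up per participant".

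In the Schedule of Activities (section 2.1), the adverse-event row is marked at D0, D1-2, D3, D4-8, D9, D10, D14 and D28. It is blank at D56 and in the last column, headed "D-90 or Early Termination".

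The visit text follows the same pattern. Section 10.1.3 (Day 28) lists "Review of AEs, clinical symptoms, and hospitalization". Section 10.1.4 (Day 56) lists only "Review of clinical symptoms, and hospitalization". Section 10.1.5 (Day 90 or early termination) has the same line plus the EQ-5D-5L.

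For participants who withdraw, section 9.1 refers to the Schedule for the data to be collected.

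The Day 28 window is ±2 days in section 2.1 and ±5 days in section 10.1.3. The safety endpoint in section 4.1 covers SAEs, and AEs that lead to stopping treatment, up to 28 days.

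Section 3.3 names immune reconstitution inflammatory syndrome (IRIS) as a possible risk of LPV/r in undiagnosed HIV-positive participants. It says "the time of onset varies from days to months after antiretroviral initiation" and requires any case to be recorded as an SAE.

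**The concern.** A site reading section 11.2.2 would ask about AEs up to the last contact. A site working from the Schedule and the visit lists would stop at Day 28 and would not ask at an early-termination contact. Both are current protocol text. Sections 9 and 11 make adherence to the Schedule mandatory, and section 11.2.2 is worded as an obligation too, so neither clearly overrides the other.

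The omission does not look like a table-reading accident. Section 10.1.3 names AEs separately from clinical symptoms, and the next two visit lists drop AEs and keep symptoms.

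At stake is the evenness of safety data. Section 12.3.2.1 compares AEs by study group, and section 7.5 says that full blinding of participants and clinicians is not feasible. If later events are recorded only when a participant volunteers them or an investigator thinks to ask, recording may differ by site and, in a trial that is not fully blinded, possibly by arm.

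**Working it through.** No power, alpha or sample-size figure is involved. The check sets the passages side by side and counts days.

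**1. Required against scheduled AE review**

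| Contact | Section 11.2.2 | Schedule AE row (2.1) | Visit text (10.1) |
|---|---|---|---|
| Day 0 to Day 14 | yes | marked | AE reporting at Day 0 and then daily to Day 14 (10.1.1, 10.1.2) |
| Day 28 | yes | marked | AE review (10.1.3) |
| Day 56 | yes | blank | symptoms, hospitalization (10.1.4) |
| Day 90 or early termination | yes | blank | symptoms, hospitalization, EQ-5D-5L (10.1.5) |

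The Schedule has no column named End of Study visit. I take it to be the Day 90 contact, or the early-termination contact for those who leave, because follow-up lasts 90 days.

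**2. Distance from the last scheduled AE review to the last contact**

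- Nominal: 90 - 28 = 62 days.
- Section 2.1 windows (D28 ±2, D90 ±5): shortest 85 - 30 = 55, longest 95 - 26 = 69 days.
- Section 10.1 windows (both ±5): shortest 85 - 33 = 52, longest 95 - 23 = 72 days.

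This is the stretch without a scheduled AE review. It does not measure lost data.

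**3. Participants who leave early**

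Up to Day 14 the AE marks are close together and section 10.1.2 lists AE reporting every day, so an event that prompts an early exit should already be on record. The next AE mark is Day 28. Someone who leaves between the two can have up to 28 - 14 = 14 days since the last scheduled AE review. The exit contact does not schedule one, and section 9.1 refers back to that same blank column. Those days lie inside the 28-day safety endpoint.

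**4. Day 28 window**

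- ±5 days: the earliest contact is Day 23, which is 28 - 23 = 5 days before the endpoint window closes.
- ±2 days: the earliest is Day 26, which is 28 - 26 = 2 days before.

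Events that could fall into this interval:

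- AEs leading to treatment discontinuation: none expected. The course is 10 days, and even the daily lists in sections 8.1.2 and 10.1.7, which show study therapy through Day 13, end well before Day 23.
- Hospitalizations: asked about again at Days 56 and 90.
- Deaths: followed to Day 90.
- Non-fatal SAEs without hospitalization: these are what mainly remains.

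**5. IRIS**

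The stated onset runs from days to months, while scheduled AE review ends at Day 28. A hospitalized case would surface at the Day 56 or Day 90 review. A case managed without admission would depend on the symptom review or on the general question in section 11.2.2.

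**The case against.** The strongest reply comes from section 11.2.2 itself. It requires a neutral question about the participant's health, and about changes since the last visit, at all study visits. It treats clinically significant reported symptoms or conditions as AEs. It also requires events reasonably possibly related to study product to be reported even after the collection period ends. Days 56 and 90 are study visits, so a look-back question there would cover Days 23 to 28 as well as the later intervals. Sections 11.2.2 and 11.2.6 name an Exit Contact Survey, and 11.2.6 says that qualifying events from the surveys are reported as AEs. Stopping treatment is not leaving the study: sections 7.3 and 9 keep such participants under evaluation, and section 7.3 follows toxicities of Grade 3 or 4 that require permanent discontinuation weekly to resolution.

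Most of this stands, and it rules out several stronger readings. A reader might infer that late harms go unrecorded, that IRIS could not be recorded as an SAE, or that the 62 days are days without safety observation. The documents do not support these, because two contacts with symptom and hospitalization review fall within that stretch and section 11.2.2 applies to both. A reader might also infer that someone leaving in the first days because of poor tolerability exits with the harm unrecorded. AE reporting is daily at that stage, so this does not follow. Nor does it follow that 5 of the 28 endpoint days are lost with a Day 23 contact; the exposure is the narrow class of event shown above.

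The reply does not remove the contradiction. The all-visits question is part of the text that the Schedule and sections 10.1.4 and 10.1.5 fail to carry through. The Exit Contact Survey has no row or day in the Schedule, section 11.1.2 names only the Daily Survey, and section 11.2.6 points to a Section 10.3 that the current numbering does not contain.

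It can also be said that shortening section 11.2.2 to 28 days would restore consistency. It would, but it would still leave the early-termination contact without an AE review, and it would sit poorly with the IRIS onset stated in section 3.3.

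**Conclusion.** The point holds as an internal contradiction with a limited consequence. Section 11.2.2 requires AE and SAE collection to the end of study. The Schedule and sections 10.1.4 and 10.1.5 schedule no AE review after Day 28 or at early termination, a nominal gap of 62 days (52 to 72 across the stated windows). Capture in that period is likely uneven rather than absent.

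The data at risk are non-hospitalized SAEs (IRIS among them) and other AEs after Day 28, and AEs in participants who leave between Days 14 and 28, where up to about 14 days may pass without a scheduled review. The two Day 28 windows add a smaller exposure of 2 or 5 days, mainly for non-fatal, non-hospitalized SAEs.

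This assumes that the End of Study visit is the Day 90 or early-termination contact and that sites give the Schedule at least as much weight as section 11.2.2. The protocol gives no rates of late AEs or of early exit, so the number of affected records cannot be estimated. The primary endpoint, sample size and power are unaffected.

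**What to change.** Reconcile the passages so that the Schedule delivers the collection period that section 11.2.2 states:

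- Add an AE/SAE mark to the D-56 and Day 90/early-termination columns in section 2.1. The row goes from 8 to 10 marked columns, and the 62-day gap closes.
- Add an AE/SAE question to sections 10.1.4 and 10.1.5. This also covers participants who withdraw, through the reference in section 9.1.
- Use one Day 28 window in sections 2.1 and 10.1.3.
- Where the Day 28 contact falls before Day 28, have the next contact ask explicitly about events through Day 28, so that the 28-day safety endpoint is observed in full.

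The cost is protocol wording and one extra question at contacts that already take place. The small downside is a few more AE records to process.

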### **11.2.3. Assessment of Adverse Events for Brazil**

#### **11.2.3.1. Intensity**

The medical assessment of intensity will be determined based on the DAIDS grading system: Grade 1 to 4.

A new event will be documented whenever the intensity of an event changes.

It is important to note the distinctions between severe AEs and severe AEs (AEs). Severity is a classification of the intensity of a specific event (such as mild, moderate, severe); however, the event itself may be of relatively secondary clinical significance (such as severe headache). An AE, however, is an AE that meets any of the specified regulatory criteria required for designating severity (eg, a headache may be severe [significantly affects the participant's usual functions], but would not be classified as severe, the unless it met any of the criteria for AEs).

#### **11.2.3.2. Causality and reporting**

The investigator will provide a causality assessment for all AEs using their best clinical judgment based on the medical information available about the event being reported. The causality assessment will be reevaluated as new information becomes available. If the investigator's assessment of causality is not reported, the event will be considered "related" until such information is received. Each investigator will assess the degree of relationship between the AE and the drugs under investigation using the following definitions:

Not related: There is no reasonable possibility that the product under investigation caused or contributed to AE.

- The event is related to a different etiology of the drug under investigation, such as underlying disease, study or procedures not included in the study, concomitant drugs or clinical status of the participant
- The timing of the occurrence of AE is not reasonably related to the administration of the study drug
- Related: There is a reasonable possibility that the product under investigation caused or contributed to the AE.
- There is no compatible temporal association between the event and the administration of the drug under investigation
- There is a biologically plausible mechanism by which study treatment may have caused or contributed to AEs
- The event improves or decreases after the study drug is discontinued without the initiation of any specific treatments for the event (withdrawal from exposure) and / or the event recurs or worsens with the reintroduction of study therapy
- The event cannot reasonably be attributed to the concomitant or underlying disease or other medications or procedures

For the purpose of assessing causality, "reasonable possibility" means that, based on the investigator's medical judgment of the available information, there are facts or arguments that suggest a positive causal relationship.

